### Sample size calculation

2.8

Sample size is recalculated based on the primary predictive objective (logistic regression for the association between PDD and PPCs). Based on the literature review of perioperative PPCs incidence in minimally invasive thoracic surgery (VATS/RATS) with standardized EPCO complication definitions and complete 7-day postoperative follow-up and our pilot study, the baseline PPC incidence of 37% was selected as the core assumption for this power analysis and sample size calculation; Assuming a PDD incidence of 30% postoperatively (7, 12), a PPCs incidence of 37% in the study population (1–5, 15, 32), an odds ratio (OR) of 3.0 for PDD predicting PPCs (7, 28), alpha = 0.05, power = 0.80, and 10% dropout rate, a minimum of 148 patients in total is required. Sample size estimation is performed using PASS software (PASS 15 Power Analysis and Sample Size Software (2017). NCSS, LLC. Kaysville, Utah, United States)^1^ with logistic regression parameters accounting for covariates (age, BMI, ASA classification), and the above parameter selection fully aligns with the literature review results of PPCs incidence in minimally invasive thoracic surgery, ensuring the consistency between clinical evidence and statistical methodology.

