### Statistical analysis

2.9

Percentages will be calculated for dichotomous data and analyzed by the Pearson chi-square test or Fisher exact test. Continuous variables will be expressed as mean standard deviation (Mean ± SD) and median (ranging from 25th to 75th percentiles), and Student’s *t*-test was used for comparison between groups; The paired sample *t*-test is used for comparison of the same index. Propensity Score Matching (PSM) will be performed to balance baseline characteristics (e.g., age, BMI, ASA classification, tumor complexity) between the VATS and RATS groups (1:1 matching ratio, caliper width 0.2 SD) to mitigate selection bias. A baseline characteristics table will be added as Table 1 in the final manuscript, which will present the demographic, clinical and surgical-related baseline data of the VATS and RATS groups before and after PSM matching, so as to clearly show the balance effect of the matching process on the baseline characteristics between the two groups. Multivariate regression models will further adjust for residual confounding variables not fully balanced by PSM. Spearman and Pearson correlation analyses are used for the correlation analysis of normal distribution variables and non-normal distribution variables, respectively. Differences in diaphragmatic function parameters (DE, DTF) across multiple time points (T0–T3) will be analyzed using Linear Mixed-Effects Models (LMM) to account for within-subject correlation of repeated measures and robustly handle missing data. Differences in DEs at different times in the same subject were assessed by the Wilcoxon signed-rank test for matched data. Associations between postoperative DE reduction and clinically significant perioperative variables were analyzed using binary logistic regression analysis and reported as estimated crude advantage ratios and relative 95% CI. Similarly, binary logistic regression with stepwise variable selection (forward method) will be used to explore risk factors for PPCs, following the “Rule of Ten” (at least 10 events per candidate variable) to avoid model overfitting. To determine the predictive power of ultrasound parameters for PPCs, ROC curve analysis will be performed to validate the predefined PDD threshold (DE < 10 mm) rather than seeking a new cut-off, evaluating its discriminatory ability for PPCs. For the correlation analysis between diaphragmatic ultrasound parameters (DE, DTF) and ARISCAT scores, Pearson correlation analysis will be adopted if both variables conform to normal distribution, and Spearman correlation analysis will be used if the distribution is non-normal. On this basis, a combined predictive model for PPCs will be constructed by integrating ultrasound parameters (DE, DTF) and ARISCAT scores, and Net Reclassification Index (NRI) and Integrated Discrimination Improvement (IDI) will be used to quantify the improvement of the combined model in the discriminatory ability of PPCs prediction compared with the ARISCAT score single-factor model; the area under the ROC curve (AUC) of the single-factor model and the combined model will be further compared to verify the predictive efficacy of the integrated approach.

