
For missing data including unmeasurable left hemidiaphragm ultrasound measurements, Multiple Imputation (MI) will be used to handle incomplete observations at any time point (T0–T3), with 20 imputed datasets generated. Listwise deletion will not be adopted to avoid selection bias and preserve statistical power. All statistical analyses were performed using SPSS software Version 26.0 (IBM, United States) and R software (Version 4.3.0) with packages “lme4” (for LMM) and “mice” (for MI).

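### No rule links forward selection of PPC risk factors to the 20 imputed datasets, and forward selection is a poor way to estimate the PDD–PPC odds ratio the study is sized on

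*Protocol article*

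**What the plan says.** Four parts of the protocol article meet here.

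- **Selection (Section 2.9).** For PPCs, "binary logistic regression with stepwise variable selection (forward method) will be used to explore risk factors for PPCs". The number of candidates is limited by a rule of "at least 10 events per candidate variable". The candidates are not listed, and no entry threshold is given.
- **Missing data (Section 2.9).** "For missing data including unmeasurable left hemidiaphragm ultrasound measurements", the plan is that "Multiple Imputation (MI) will be used to handle incomplete observations at any time point (T0–T3), with 20 imputed datasets generated". It adds that "Listwise deletion will not be adopted to avoid selection bias and preserve statistical power". The R package for imputation is named. No rule is given for selecting variables or combining estimates across the 20 datasets.
- **Objective (Section 2.6.1).** The primary objective is to describe PDD incidence and to explore its association with PPCs.
- **Sample size (Section 2.8).** The 148 patients rest on a logistic regression of PPCs on PDD, with age, BMI and ASA classification as covariates: "Assuming a PDD incidence of 30% postoperatively", "a PPCs incidence of 37% in the study population", an odds ratio of 3.0, alpha 0.05, power 0.80 and 10% dropout.

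**The concern.** Rubin's rules average the same coefficient over all imputed datasets, so the same model must be fitted in each. Forward selection makes the model a function of the data. The ultrasound measures are the study's main candidate predictors and also the variables expected to have gaps, so each imputed dataset carries different values of DE, and hence of PDD. Run separately, selection may return different variable lists. Without a stated rule, someone must settle after seeing the results which list counts and how its odds ratios are combined.

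A second issue exists even with complete data. The study is sized to estimate one association, PDD with PPCs. Section 2.9 describes no logistic model in which PDD is held in place with the covariates named in Section 2.8. Its multivariable risk-factor regression for PPCs is the forward-selected one. There PDD can drop out, in which case the paper reports no adjusted odds ratio for it. If it stays, it does so because its estimate was large enough to enter, which biases the reported value upward.

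**Working it through.** **1. Reproduce the sample size.** The inputs from Section 2.8 are PDD prevalence 0.30, overall PPC incidence 0.37 and OR 3.0. Solving 0.7·p0 + 0.3·p1 = 0.37 with an odds ratio of 3 gives p0 = 0.292 and p1 = 0.553. The unit variance of the log odds ratio is

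V = 1/(0.7 × 0.292 × 0.708) + 1/(0.3 × 0.553 × 0.447) ≈ 6.91 + 13.48 = 20.4.

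With two-sided alpha 0.05 (sidedness is not stated),

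n = (1.960 + 0.842)² × V / (ln 3)² = 7.85 × 20.4 / 1.207 ≈ 132.6,

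and 132.6 / 0.90 = 147.4, which rounds up to 148. The stated figure reproduces, with about 133 evaluable patients. This is one route to 148. The article does not show the software settings.

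**2. Room for covariates.** Expected events are 133 × 0.37 = 49 to 148 × 0.37 = 55. At ten events per term that allows 4 to 5 terms. PDD, age, BMI and ASA as a single term make four.

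**3. Agreement between imputed datasets.** Simulations used PDD 30%, PPC about 37%, OR 3.0, 20 proper imputations with PPC in the imputation model, and forward selection run separately in each dataset at p < 0.05. The threshold, the candidates and all missing rates are assumptions. Setting A had 133 patients, PDD plus three weak predictors, and only day-1 DE missing (300 trials per rate). Setting B had five candidates (PDD, DTF, an ARISCAT-like score, age, approach), with DE and DTF both missing (400 trials per rate). Setting C was a further run with 133 patients and day-1 DE missing. Monte Carlo error is about 3 points.

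Trials in which the 20 datasets did not all select the same model:

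| Missing | A (n=133) | B (n=148 / 133) | C (n=133) |
|---|---|---|---|
| 0% | – | 0% / 0% | – |
| 5% | 32% | 47% / 43% | 38% |
| 10% | 42% | 68% / 64% | 49% |
| 20% | 65% | 80% / 82% | 67% |

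Trials in which PDD was kept in some but not all datasets:

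| Missing | A | B (n=148 / 133) | C |
|---|---|---|---|
| 5% | 23% | 23% / 20% | 29% |
| 10% | 27% | 34% / 34% | 38% |
| 20% | 51% | 50% / 54% | 51% |

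Overall disagreement depends strongly on the candidate set. Instability of PDD itself varies less.

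**4. Selection with complete data.** At n = 133 the standard error of the log odds ratio is √(20.4/133) = 0.392, so entry at p < 0.05 needs a log odds ratio above 1.960 × 0.392 = 0.768, an OR of about 2.15. The true value is ln 3 = 1.099, which lies (1.099 − 0.768)/0.392 = 0.845 standard errors above that line. PDD therefore enters in about 80% of trials and is left out in about 20%, which is the planned power restated. Given entry, the mean log odds ratio is 1.099 + 0.392 × 0.279/0.801 = 1.235, where 0.279 is the normal density at 0.845 and 0.801 the entry probability. That is an OR of about 3.4 where the truth is 3.0. Simulation gave the same picture: a mean of about 3.6 when selected against 3.1 overall.

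**The case against.** **The text does not prescribe selection within each dataset.** This is right. Selection on pooled tests combines properly with imputation, and so does a selection-frequency rule followed by refitting one common model in all 20 datasets. A reader might infer that the two methods contradict each other and that no single set of odds ratios can exist. The documents do not support that. They leave open how the methods join, and a statistical analysis plan that is not shown could close the gap.

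**The model is exploratory.** Section 2.9 says so by its choice of verb, and Section 2.6.2 makes risk-factor identification a secondary objective. A reader might infer that the odds ratio behind the 148 patients must come from the stepwise model, or that this is the only PPC model. Neither is stated. Section 2.8 describes a regression with named covariates and does not mention selection. Section 2.9 also plans an ARISCAT plus DE/DTF prediction model and a ROC analysis of the 10 mm threshold, neither of which uses forward selection.

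**Missingness may be low.** Patients without satisfactory imaging are excluded (Section 2.2), and an unmeasurable left side shifts analysis to the right (Section 2.3.1). That is fair, and no rate is given. Yet the plan itself expects unmeasurable readings and blocked windows, and disagreement was already 32–47% at 5% missing.

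What remains is the second issue, which does not depend on missing data. Section 2.9 does not carry the model described in Section 2.8 into the analysis. The only multivariable risk-factor regression for PPCs that it describes is one in which PDD may not survive.

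**Conclusion.** The point holds as a worthwhile, inexpensive improvement, not as a fatal flaw.

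- If selection is run per dataset, expect disagreement between imputed datasets in roughly 30–80% of trials at 5–20% missing, and PDD kept in only some datasets in roughly 20–54%. These figures rest on assumed missing rates, candidates, effect sizes and a 5% entry threshold. They fall to zero with complete data and do not apply if selection uses pooled tests.
- Regardless of missing data, and assuming PDD is a candidate entered at 5%, forward selection would omit it in about one trial in five under the plan's own assumptions. When PDD is kept, its odds ratio would be overstated by about 15% (3.4 against 3.0 by formula, 3.6 against 3.1 in simulation).

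A reader might take this to threaten the main result. It does not: the primary endpoint, day-1 PDD incidence, involves no variable selection, and the separate ARISCAT plus DE/DTF model has fixed inputs.

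**What to change.** In Section 2.9, or in the statistical analysis plan:

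1. Estimate the PDD–PPC association with one prespecified logistic model: PDD forced in, plus age, BMI and ASA class, matching Section 2.8. State how ASA is coded. As one term the model has four terms. As two indicators it has five, which is 49/5 = 9.8 events per term at 133 patients and 55/5 = 11 at 148.
2. Fit that same model in all 20 imputed datasets, include PPC in the imputation model, and pool by Rubin's rules.
3. If a data-driven list of risk factors is still wanted, keep it as a secondary analysis labelled exploratory, with selection based on pooled Wald tests.

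The cost is wording only: no extra patients or data, and the software already named is sufficient. The downside is that the covariates must be fixed in advance, so a strong predictor outside the list would appear only in the exploratory analysis.

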However, postoperative diaphragmatic dysfunction (PDD), as a potential risk factor for PPCs, has not been fully recognized in lung resection. The term diaphragmatic dysfunction includes eventration, weakness and diaphragmatic paralysis (9). The diaphragm is the primary inspiratory muscle, and its function directly affects postoperative respiratory mechanics and expectoration ability. Studies have shown that the incidence of PDD after thoracic surgery can be as high as 12.5–68%, and it is closely related to PPCs such as pulmonary infection and atelectasis (7, 10, 11). Traditional diagnosis includes radiography, fluoroscopy, pulmonary function tests, and stimulation of the phrenic nerve, with some limitations including exposure to ionizing radiation, intense patient cooperation and less sensitivity or specificity. However, point-of-care ultrasound (POCUS) offers a noninvasive and dynamic approach to assess perioperative diaphragmatic function. Ultrasound has shown to be useful for the detection of diaphragmatic dysfunction, with a high sensitivity (93%) and specificity (100%) for diaphragmatic neuromuscular disease, and it has been suggested as the technique of choice for assessing diaphragmatic movement on suspicion of malfunctioning (9). Spadaro et al. first introduced POCUS in thoracic surgery. They defined DD as diaphragmatic excursion (DE) < 1 cm and demonstrated an increased risk of PPCs in patients with early PDD (OR = 5.5) (7). Recent evidence further highlights a lower postoperative diaphragmatic excursion difference (DED) after video-assisted thoracoscopic surgery (VATS) can serve as an additional marker, which helps predict the risk of PPCs (11). Additionally, Daniel et al. reported that PDD predominantly occurs on the surgical side, persists until postoperative 3rd day, and independently prolongs hospital stays (OR = 1.3) (12). Diaphragmatic thickness (DT) and thickening fraction (DTF) are also critical metrics; DT reduction >10% or DTF <20% are defined as thresholds for clinically relevant atrophy in critically ill patients according to an expert consensus in 2022 (13), with the point that preoperative diaphragmatic atrophy (DT < 0.2 cm) significantly increases PPCs risk.

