Some studies suggest that the outcomes of RATS are similar to or even better than those of VATS surgery (5, 14). Geraci et al. reported that the incidence of early postoperative complications in 253 patients who underwent RATS lung resection was only 6.4% (15). However, this study lacked long-term follow-up and the definition of PPCs may differ from that in many previous studies, which may have resulted in an underestimation of the incidence of PPCs. RATS, with its three-dimensional high-definition vision, flexible instruments and tremor filtering function, theoretically can reduce the intraoperative traction of the phrenic nerve and chest wall trauma (16); however, RATS-specific intraoperative factors such as CO2 insufflation (capnothorax) induce an artificial increase in intrathoracic pressure, which exerts direct mechanical and physiological effects on the diaphragm: the elevated intrathoracic pressure antagonizes the abdominal-to-thoracic pressure gradient generated by diaphragmatic contraction, directly reducing the effective excursion amplitude of the diaphragm; sustained intrathoracic hypertension compresses the intrathoracic microvasculature, impairs local microcirculatory perfusion of the diaphragmatic muscle fibers, and hinders oxygen supply and metabolite excretion of the muscle tissue; in addition, the diaphragm needs to maintain a higher contractile tension to overcome the increased intrathoracic pressure during the surgical period, which easily induces early fatigue of the diaphragmatic muscle fibers. These changes may alter diaphragmatic excursion and contractility in the perioperative period, in contrast to VATS, which does not require artificial CO2 insufflation to establish a pneumothorax and maintains intrathoracic pressure at a physiological level without the above-mentioned diaphragm function interference factors—an aspect rarely addressed in previous studies. Patients can be discharged on the first day after RATS lung resection, and both the clinical effect and patient satisfaction are excellent (15). Early research by Mahieu et al. showed that the proportion of emergency conversion to thoracotomy during RATS was significantly lower than that of traditional video-assisted thoracoscopic surgery (VATS) (3.6% vs. 14.3%), suggesting its potential safety advantage (17). Despite these advances, current studies predominantly focus on single-timepoint assessments of diaphragmatic function or single minimally invasive surgical modality, lacking longitudinal data comparing VATS and RATS across the perioperative period.

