#### Primary

2.6.1

To describe the incidence of postoperative diaphragmatic dysfunction (PDD) and explore its association with postoperative pulmonary complications (PPCs) after minimally invasive thoracic surgery (VATS and RATS).

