#### Secondary

2.6.2

To identify potential risk factors (such as surgical technique) of PPCs and to evaluate the clinical application of diaphragm ultrasound examination.

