## Discussion

4

The higher incidence of PPCs in thoracic surgery patients is significantly associated with PDD (7, 9, 11, 35). We will use POCUS to specifically investigate the correlation between these two factors in minimally invasive surgery patients. As surgical techniques have evolved, the opportunities for clinical applications of RATS in thoracic surgery are increasing. In fact, according to a review of the Society for Thoracic Surgery General Thoracic Surgery Database 2023 (STS-GTSD), more than 80% of lobectomies, segmental resections, and wedge resections are performed through minimally invasive approaches (5). The feasibility of RATS lobectomy has been confirmed by several relevant studies in the last 5 years; compared to open thoracotomy, RATS seems to offer the same advantages as the VATS access (16). We will further evaluate the effects of these two surgical approaches on diaphragm function in surgical patients.

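### If PDD is selected in the stepwise PPC model, the technique coefficient omits any effect acting through the diaphragm, and no other analysis is assigned to the objective on technique

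*Protocol article*

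**What the plan says.** - **Technique as a target.** The secondary objective (2.6.2) is "To identify potential risk factors (such as surgical technique) of PPCs", and technique is the only example it names.
- **PDD as a predictor.** The primary objective (2.6.1) is to describe the incidence of PDD and "explore its association with postoperative pulmonary complications (PPCs) after minimally invasive thoracic surgery (VATS and RATS"). The Introduction presents "postoperative diaphragmatic dysfunction (PDD), as a potential risk factor for PPCs". The sample size (2.8) rests on an OR of 3.0 for PDD on PPC.
- **The risk-factor analysis.** Section 2.9 states that "binary logistic regression with stepwise variable selection (forward method) will be used to explore risk factors for PPCs", subject to "at least 10 events per candidate variable". The candidates are not listed.
- **Technique and the diaphragm.** On capnothorax during RATS, the Introduction says: "These changes may alter diaphragmatic excursion and contractility in the perioperative period, in contrast to VATS". The Discussion adds: "We will further evaluate the effects of these two surgical approaches on diaphragm function in surgical patients".
- **A second route for technique.** Section 2.9 also plans 1:1 propensity matching of the VATS and RATS groups on baseline characteristics, followed by regression for residual confounding. It names no outcome for this comparison.

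**The concern.** The Introduction links the diaphragm to PPCs in one place and technique to the diaphragm in another. Together these make PDD a possible step between technique and PPCs. A model that contains both an exposure and its intermediate estimates only what the exposure does by other routes. For technique, that leaves out the route the authors themselves discuss.

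Forward selection adds a difficulty: the data decide whether PDD is in the model, and so which effect of technique is reported. A technique coefficient near the null, or technique not being selected, could then be read as showing that technique is not a risk factor for PPCs, when the model has only shown little effect beyond PDD. The article nowhere separates the total from the direct effect of technique.

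**Working it through.** **1. The plan's own figure.** Inputs from 2.8: PDD 30%, PPC 37%, OR 3.0, alpha 0.05 (taken as two-sided), power 0.80, dropout 10%. Taking 37% as the overall PPC rate, the risks p0 (no PDD) and p1 (PDD) solve 0.70·p0 + 0.30·p1 = 0.37 with an odds ratio of 3.0. This gives p0 = 0.2917 and p1 = 0.5527. The Wald formula for a binary covariate is

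N = (1.960 + 0.842)² × [1/(0.70·p0(1−p0)) + 1/(0.30·p1(1−p1))] / (ln 3)²

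It gives 133, and 133/0.90 rounds up to 148. The stated figure is reproduced, so these inputs are a fair base for what follows.

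**2. Room for both candidates.** Expected PPC events are 148 × 0.37 = 54.8, or 148 × 0.90 × 0.37 = 49.3 after dropout. At ten events per candidate, four or five candidates are allowed. Technique and PDD can both be among them.

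**3. Total versus PDD-adjusted effect.** Assumptions not in the documents: half the patients have RATS, there is no confounding, the technique–PDD OR is 1.5 to 4, and technique acts on PPC only through PDD. For an arm with PDD risk p,

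P(PPC) = p × 0.5527 + (1 − p) × 0.2917

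| Technique–PDD OR | PDD in the two arms | PPC in the two arms | Total OR | OR with PDD in model |
|---|---|---|---|---|
| 1.5 | 25.8% / 34.2% | 35.9% / 38.1% | 1.10 | 1.00 |
| 2 | 22.8% / 37.2% | 35.1% / 38.9% | 1.17 | 1.00 |
| 3 | 18.9% / 41.1% | 34.1% / 39.9% | 1.28 | 1.00 |
| 4 | 16.3% / 43.7% | 33.4% / 40.6% | 1.36 | 1.00 |

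If technique also has a direct OR of 1.5, the total OR runs from 1.61 to 2.00 over the same range, and the PDD-adjusted OR is 1.50. The adjusted coefficient is then reduced, not abolished.

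**4. What forward selection does.** This was simulated with 148 patients, PDD and technique as the only candidates, likelihood-ratio entry at p < 0.05, and 1,500 runs per setting.
- Wholly indirect effect, technique–PDD OR 2 or 3: PDD was selected in about 85% of runs and technique in about 5%, the false-positive rate. The median technique OR was 1.18 to 1.27 without PDD and 0.97 to 1.00 with it.
- Technique–PDD OR 3 plus a direct OR of 1.5: technique was selected in 22% of runs. Its median OR fell from 1.87 without PDD to 1.49 with it.

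**5. Power without PDD in the model.** With 74 patients per group, a wholly indirect effect has power of about 7%, 11% and 15% for technique–PDD ORs of 2, 3 and 4.

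**The case against.** - **The candidates are not listed.** This is true, and a condensed article may leave the list to a fuller document, so its absence is not the point. That both variables are candidates is an inference. It is a strong one, because technique is the named example in the objective and PDD is the predictor on which the study is sized.
- **The matched comparison may already answer the question.** Matching on baseline characteristics does not condition on PDD. Applied to PPCs, it would estimate the total effect. A reader might infer that the effect through the diaphragm is lost from the whole study; the documents do not support that. The loss is confined to the risk-factor model, and only when PDD is selected. What remains is that 2.9 neither names PPCs as the outcome of the matched comparison nor assigns the 2.6.2 objective to it.
- **The pathway is assembled from separate statements.** This is also true. The capnothorax argument stops at the diaphragm, and the link to PPCs comes from elsewhere in the Introduction. The same discussion says RATS may reduce traction on the phrenic nerve and chest wall trauma, so the net direction is open. Nothing in the article claims that PDD carries the whole effect.
- **The practical loss is small and the aim exploratory.** With power of about 7% to 15%, leaving PDD out would rarely make a wholly indirect effect significant. That stands. But the quantity estimated still differs: with PDD in the model the estimate centres on 1.0 at any sample size, whereas without PDD it centres on the total effect, with an interval showing how little is known.

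**Conclusion.** The point holds in a limited form. The one analysis tied to PPC risk factors very likely offers both technique and PDD as candidates. When PDD enters, technique's coefficient is a direct effect and tends toward the null for any part acting through the diaphragm. Under a wholly indirect effect, a total OR of about 1.1 to 1.4 becomes 1.0. With a direct OR of 1.5 as well, 1.61 to 2.00 becomes 1.50.

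These sizes use the planned PDD and PPC rates and OR of 3.0. They also rest on assumptions that the documents do not give: an even split of approaches, no confounding (including none between PDD and PPC), and the chosen technique–PDD ORs.

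A reader might infer that the study is bound to conclude that technique is not a risk factor. The documents do not support that: PDD is often but not always selected, a direct effect would remain visible, and the matched comparison may give the total effect. The PDD–PPC estimate is not affected, since technique is a possible confounder there and may properly be adjusted for. The ARISCAT prediction model is not affected either, since an intermediate is acceptable in a prediction model.

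**What to change.** In 2.9:
1. State that the secondary objective on technique is answered from the propensity-matched VATS versus RATS comparison, or from a prespecified regression on preoperative covariates, with PPC as the outcome and no postoperative ultrasound variable in the model.
2. Estimate PDD on PPC in a separate prespecified model, adjusted for technique and preoperative covariates.
3. Label any technique OR from a model containing PDD or another postoperative diaphragm measure as a direct effect.
4. Report the total effect with its confidence interval, and say that the study has little power for an effect acting only through the diaphragm.

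The cost is a few sentences and at most one additional model. No new data are needed, since 2.10 already records surgical approach and the preoperative covariates. The sample size does not change.
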